# Clinical Application of Radioembolization in Hepatic Malignancies: Protocol for a Prospective Multicenter Observational Study

**DOI:** 10.2196/16296

**Published:** 2020-04-22

**Keywords:** hepatocellular carcinoma, metastasis, observational study, registries, therapeutic embolization, liver, yttrium-90, radioisotope brachytherapy

## Abstract

**Background:**

Radioembolization, also known as transarterial radioembolization or selective internal radiation therapy with yttrium-90 (90Y) resin microspheres, is an established treatment modality for patients with primary and secondary liver tumors. However, large-scale prospective observational data on the application of this treatment in a real-life clinical setting is lacking.

**Objective:**

The main objective is to collect data on the clinical application of radioembolization with 90Y resin microspheres to improve the understanding of the impact of this treatment modality in its routine practice setting.

**Methods:**

Eligible patients are 18 years or older and receiving radioembolization for primary and secondary liver tumors as part of routine practice, as well as have signed informed consent. Data is collected at baseline, directly after treatment, and at every 3-month follow-up until 24 months or study exit. The primary objective of the Cardiovascular and Interventional Radiological Society of Europe Registry for SIR-Spheres Therapy (CIRT) is to observe the clinical application of radioembolization. Secondary objectives include safety, effectiveness in terms of overall survival, progression-free survival (PFS), liver-specific PFS, imaging response, and change in quality of life.

**Results:**

Between January 2015 and December 2017, 1047 patients were included in the study. The 24-month follow-up period ended in December 2019. The first results are expected in the third quarter of 2020.

**Conclusions:**

The CIRT is the largest observational study on radioembolization to date and will provide valuable insights to the clinical application of this treatment modality and its real-life outcomes.

**Trial Registration:**

ClinicalTrials.gov NCT02305459; https://clinicaltrials.gov/ct2/show/NCT02305459

**International Registered Report Identifier (IRRID):**

DERR1-10.2196/16296

## Introduction

Primary hepatic malignancies are among the most common cancers of solid organs worldwide and are the fourth to fifth leading cause of death. From the primary liver diseases cirrhosis and hepatocellular carcinoma (HCC), about 180,000 and 75,000 patients, respectively, will die per year in Europe [1,2]. Significant rises in incidence rates for hepatic inflammation, fibrosis, and cirrhosis—predisposing factors for HCC—are expected for the next decade with causes such as autoimmune disease, drug-related effects, or nonalcoholic fatty liver disease [2]. About 4 million people per year are affected by cancer in Europe; 30% to 80% of these patients might develop hepatic metastases [3].

Curative treatment of a hepatic malignancy by liver transplantation, resection, and local ablation can be applied in only about 10% to 25% of cases. Unfortunately, the vast majority of patients do not qualify for these therapies. Various kinds of systemic treatments including chemotherapy, biological therapy, and cancer immunotherapy are offered to this group of patients [4-7]. There is a substantial subset of patients with liver-limited disease that are not suitable for surgical or percutaneous ablative therapies, who experienced early recurrences or no response, significant side effects, or intolerance when treated with systemic therapies. In this setting, transarterial therapies such as chemoembolization, chemoperfusion, or radioembolization (eg, selective internal radiation therapy or transarterial radioembolization) may offer substantial therapeutic improvement [4,7]. Furthermore, these therapies may allow a reduction of systemic side effects, extend periods of freedom from chemotherapy, and prime the liver for other potential local treatment options such as surgery or local ablation [8-11].

Several current, large-scale randomized controlled trials (RCTs) could define the role of radioembolization in first-line and second-line therapy regimens in more advanced primary and secondary liver malignancies [12-15]. Based on this data, current guidelines suggest radioembolization should be considered as a component of the “tool-box” [5,6] in the treatment of HCC, cholangiocarcinoma, and metastatic colorectal cancer (mCRC) following progression after standard therapies or intolerance to other therapies [4,16].

Nevertheless, there is still limited information and understanding of the application of radioembolization in a real-life clinical setting [13,17]. Recent observational studies conducted in the United Kingdom describe the outcome of the real-life application of radioembolization in patients with colorectal liver metastases and intrahepatic cholangiocarcinoma [18,19]. However, similar real-world data from other countries and from patients with other liver malignancies such as HCC are needed by physicians, patients, and paying bodies. More observational data on the use of radioembolization in various clinical settings would elucidate the position of radioembolization in clinical practice and additionally provide data for less established uses of radioembolization, as in metastatic liver disease from other primaries (eg, breast cancer, malignant melanoma, or pancreatic cancer) [20,21].

To further improve the understanding of the real-life clinical application of radioembolization and its impact on clinical practice, the Cardiovascular and Interventional Radiological Society of Europe (CIRSE) initiated the *CIRSE Registry for SIR-Spheres Therapy (CIRT)* for patients treated with radioembolization with yttrium-90 (90Y) resin microspheres (SIR-Spheres, Sirtex Medical Pty Limited; St. Leonards, NSW, Australia). CIRT will collect data on how radioembolization is embedded in real-life clinical practice as well as effectiveness, safety, technical considerations, and patient-reported quality of life (QOL).

## Methods

### Study Design and Objectives

CIRT is a prospective, multicenter, single-device, noninterventional study of patients with liver tumors treated with radioembolization in daily routine practice as a standard of care. The primary objective is to observe the real-life clinical application of radioembolization and the impact of the treatment in clinical practice. This objective is described by: type of liver cancer, intention of treatment, prior hepatic procedures, associated systemic therapy, and postradioembolization hepatic procedures.

Secondary objectives are effectiveness, safety, technical considerations, and patient-reported outcome measures (see Textbox 1).

Secondary end points.
**Effectiveness end points**
Overall survivalProgression-free survivalHepatic progression-free survival (ie, liver-specific progression-free survival)Imaging response
**Safety end points**
Day-of-treatment complicationsAdverse eventsLaboratory values
**Technical considerations end points**
Patient-related characteristicsTreatment-related characteristicsTreatment administrationProcedure-related outcomes
**Patient-reported outcome end points**
Quality of life questionnaire C30Additional hepatocellular carcinoma module for patients with hepatocellular carcinoma

### Site Selection and Patient Enrollment

Sites that incorporated radioembolization in their standard of care armamentarium and had a minimum amount of experience with the procedures were considered for invitations to participate in the study (ie, 10 or more treatments in the last 12 months and a career history of at least 40 cases). The selected sites were limited to centers in the European Union, Switzerland, Turkey, and Israel. A multidisciplinary steering committee containing experts from the field of medical oncology, diagnostic and interventional radiology, hepatology, surgery, and nuclear medicine developed a list of sites that met the selection criteria and continued to update this list throughout the course of the study. All sites that met the selection criteria were invited directly by the steering committee.

Eligible patients consist of any adult patients treated with radioembolization with 90Y resin microspheres for primary or secondary liver tumors that have signed the informed consent form. No formal sample size calculation was made. The steering committee reasoned that about 1000 patients could be recruited during a period of 3 years, and this would be sufficient to observe the real-life clinical application of radioembolization.

Site enrollment was from August 2014 until April 2017. Patients were included from January 2015 until December 2017. Follow-up data collection ended in December 2019.

This study was performed in accordance with the Declaration of Helsinki and Good Clinical Practice Guidelines. This study was approved by the local ethics committees of participating centers.

### Data Collection

Patients enter the study by accepting participation and signing the informed consent form. Baseline data is collected upon allocation. Data on how the treatment was performed and its day-of-treatment outcomes are collected on the day of treatment. The patient is then followed for a maximum of 24 months or until study exit (see Figure 1). Guidelines for radioembolization advise that posttreatment assessments should be performed every 3 months [22]. However, the final decisions on treatment and follow-up schedules are determined by the site-specific medical teams.

Baseline assessments included patient demographics, medical history related to the underlying disease and cancer treatment, as well as cancer type and stage for patients with HCC (Table 1). The technical aspects that may determine how radioembolization is performed or impacts procedure-related outcomes were documented at the time of treatment. Time to event end points and safety end points were collected at every follow-up. In addition to demographic and clinical data, patient-reported outcomes are measured using the European Organisation for the Research and Treatment of Cancer (EORTC) quality of life questionnaire C30 (QLQ-C30) [23,24]. The questionnaire was provided before the treatment, shortly after the treatment, and at every follow-up. When this was not feasible on site, patients were approached via letters or phone calls organized by the study center responsible for the patient. For patients with HCC, in addition to the QLQ-C30, the HCC module was provided to assess factors related to chronic liver disease, as well as issues related to the primary tumor and its treatment [25]. The QLQ-C30 and HCC module were made available to each patient in their local language, using questionnaires translated and validated by EORTC [26-28].

Demographic and clinical data obtained from medical examinations, medical records, and QOL forms were transferred into an electronic case report form (e-CRF). Patient data was pseudonymized by each site without a centralized pseudonymization policy, and data collection was done according to the General Data Protection Regulation and stored in an encrypted form on a state-of-the-art server in Vienna, Austria. The e-CRF was accessible through a custom-built online database developed by ConexSys Inc (Lincoln, RI) and installed on the CIRSE server in Vienna, Austria. Access to the system is password protected. Statistical analysis will be performed by an independent statistician.

Data quality was ensured through regular remote monitoring of data entered into the database. Remote monitoring includes regular information on data quality (query reports), inclusion of patients, and follow-ups. No on-site monitoring or source data verification was performed due to limited resources.

**Figure 1 figure1:**
[figure not shown]
Flowchart of patient inclusion and measurement time points. CIRT: Cardiovascular and Interventional Radiological Society of Europe Registry for SIR-Spheres Therapy.

**Table 1 table1:** Time of measurement for each end point and associated measurements.

End point	Baseline measurement	Day of treatment measurement	Follow-up measurement
Real-life application of radioembolization	Type of liver cancer Prior hepatic procedures Associated systemic therapy (prior systemic therapy)	Intention of treatment	Postradioembolization hepatic procedures Postradioembolization systemic chemotherapy
Effectiveness end points	N/A^a^	Treatment date	Date of effectiveness event (OS^b^, PFS^c^, hepatic PFS, IR^d^)
Safety end points	N/A	Severe day of treatment complications (Grade 3-4)^e^	Adverse events (Grade 1-5)^e^ Abnormal laboratory values
Technical considerations end points	Patient-related characteristics Prior hepatic procedures Physical characteristics (body surface area, lung shunt study [%], Eastern Cooperative Oncology Group performance status)	Treatment planning Treatment administration Procedure-related outcomes	N/A
Patient-reported outcome end points	EORTC^f^ QLQ-C30^g^ Additional module for HCC^h^	N/A	EORTC QLQ-C30 Additional module for HCC

^a^N/A: not applicable.

^b^OS: overall survival.

^c^PFS: progression-free survival.

^d^IR: imaging response.

^e^Grading according to Common Terminology Criteria for Adverse Events version 4.03.

^f^EORTC: European Organisation for the Research and Treatment of Cancer.

^g^QLQ-C30: Quality of Life Questionnaire C30.

^h^HCC: hepatocellular carcinoma.

### Statistical Analysis

All patients who were found eligible, enrolled in the registry, underwent radioembolization treatment, and have the minimum amount of data required will be included in analysis. Patients for which the amount of data collected is too scarce to warrant meaningful analysis will be excluded. The number of excluded patients and reason for exclusion will be reported.

Data regarding the primary end point, safety, and technical considerations will be presented by summaries (eg, counts, means, standard deviations) and descriptive statistics. The number of missing observations will be given in all summary tables. Time to event end points will be described graphically through the Kaplan-Meier analysis (including 95% CIs for median survival). The Cox regression will be used to assess the impact of the covariates for time to event end points (Table 2).

Hazard ratios and their 95% CIs will be presented together with *P* values. Sensitivity analyses of time to event data will be performed where censored patients with less than 6 weeks of follow-up will be included as worst case (ie, death or progression).

**Table 2 table2:** Covariates for time to event end points.

Covariate	Variables
Age (years)	≤69 and ≥70
Sex	Male, female
Number of lines of previous chemotherapy	0, 1, 2-5, ≥6
Primary tumor in situ	Yes, no
Eastern Cooperative Oncology Group performance status	0, 1, and ≥2
Presence of extrahepatic metastases	Yes, no
Prior liver procedures	Yes, no
Number of liver tumors	1, 2-5, and ≥6
Percentage tumor to liver volume	Continuous

QOL is measured with the EORTC QLQ-C30, a questionnaire developed to assess the QOL in patients with cancer. The QLQ-C30 includes five functional scales, three symptom scales, a global health status scale, and six single items. The functional and symptom status of the QLQ-C30 will be assessed according to the scoring manual developed and validated by EORTC [29]. Patients who die during follow-up will be included in the QOL analyses until their date of death. The focus of these analyses will be on patients who are alive at the time point of analysis.

To document the safety and effectiveness of radioembolization and subsequent surgical or interventional procedures, the data will be broken down into subgroups as defined for the covariate analyses above.

Missing data can be expected in the event of a study site failing to enter certain data into the e-CRF, or a patient’s withdrawal of consent or being lost to follow-up. Given the descriptive and exploratory nature of CIRT, all available data will be used, and no imputations of missing data will be made. The amount of missing data will be summarized and the subset of patients with missing data will be compared with patients included in the analysis.

In the effectiveness analyses, patients withdrawing consent or being lost to follow-up will be censored at the last time they were observed as being alive (overall survival) or at the time of their last magnetic resonance imaging scan from which disease progression could have been determined (progression-free survival [PFS]). Patients who die during the course of their follow-up in the registry will be regarded as having disease progression in the analyses of PFS and liver-specific PFS.

Missing data for QOL will be handled in line with the suggestions in the EORTC scoring manual for QLQ-C30; the amount of and reasons for completely missing forms will be analyzed and multiple imputations will be used for a part of the completely missing forms (ie, forms considered to be missing at random or due to administrative failure) [29].

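### Excluding treated patients for scarce data has no limit to facts known at treatment, so it can select on early death or loss and weaken the 6-week worst-case analysis

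*Protocol article*

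**What the plan says.** The protocol article defines one analysis population under Statistical Analysis. Patients who were eligible, enrolled and treated and who "have the minimum amount of data required will be included in analysis". The next sentence gives the reverse: "Patients for which the amount of data collected is too scarce to warrant meaningful analysis will be excluded". Neither sentence names an endpoint, so both apply to overall survival (OS), progression-free survival (PFS) and safety as well as to the descriptive tables. On disclosure: "The number of excluded patients and reason for exclusion will be reported".

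The same section contains three other rules that bear on patients with little data:

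- Missing data: "all available data will be used, and no imputations of missing data will be made".
- Censoring for OS: "patients withdrawing consent or being lost to follow-up will be censored at the last time they were observed as being alive". For PFS, censoring is at the last scan that could have shown progression. Deaths during follow-up count as progression.
- Sensitivity analysis: "censored patients with less than 6 weeks of follow-up will be included as worst case", that is, as a death or a progression.

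It also plans that "the subset of patients with missing data will be compared with patients included in the analysis". The Limitations section adds a baseline comparison of lost and followed patients, with further analyses if a notable difference appears.

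**The concern.** How much data a treated patient accumulates depends partly on how long that patient lives and stays under observation. Table 1 places effectiveness event dates, graded adverse events and abnormal laboratory values at follow-up only; on the treatment day the safety item is severe complications. Data Collection describes guideline-advised follow-up at 3-month intervals, with the schedule left to the sites. A patient who is treated and not seen again therefore has baseline and treatment-day data and little else. A rule that removes patients by volume of data can thus make entry to the survival and safety analyses depend on what happened after treatment.

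The stake is the absolute estimate. The registry has one arm and no comparator, and it aims to describe outcomes in routine practice. If the removed patients did worse than the rest, OS and PFS would look better than they were, and early adverse events could be under-counted. No second arm would offset the error.

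**Working it through.** **1. No figure in the plan to reproduce.** The article gives no expected survival, no expected exclusion rate and no formal sample size calculation. The check is therefore a comparison of the rules, followed by an illustration under stated assumptions.

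**2. One patient under each rule.** Take a patient treated, last seen alive at week 4, then lost.

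| Rule (Statistical Analysis) | What happens to the patient |
|---|---|
| Data-scarcity exclusion | May be removed from every analysis |
| All available data used | Kept |
| Censoring of lost patients | Kept, censored at week 4 for OS |
| 6-week worst case | Kept, counted as an event |

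The article does not say which rule comes first. If the exclusion does, the worst-case analysis cannot reach this patient.

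**3. Illustration: the excluded are the earliest deaths.** Inputs: N = 1047 (Results) and 24 months of follow-up (Data Collection). Assumed: exponential OS with true median m, and an excluded share f. Removing the earliest share f of deaths leaves S(t)/(1 − f), so

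- new median = m × [1 − log2(1 − f)]
- new 12-month OS = S(12)/(1 − f)

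For m = 12, S(12) = 50%:

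| f (patients) | Median, formula | Median, simulated | 12-month OS |
|---|---|---|---|
| 2% (21) | 12 × 1.029 = 12.35 | 12.3 | 0.50/0.98 = 51.0% |
| 5% (52) | 12 × 1.074 = 12.89 | 12.9 | 0.50/0.95 = 52.6% |
| 10% (105) | 12 × 1.152 = 13.82 | 13.8 | 0.50/0.90 = 55.6% |

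The simulated column is the mean Kaplan-Meier median over 300 replicates. The relative rise (about 3%, 7% and 15%) does not depend on m. The simulated medians go from 8 to 8.2, 8.6 and 9.3 months, and from 18 to 18.5, 19.3 and 20.8.

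**4. Illustration: the excluded were lost within 6 weeks.** Simulated, m = 12, f = 5%:

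| Reason for loss | Keep and censor | Exclude | Keep, 6-week worst case |
|---|---|---|---|
| Unrelated to prognosis | 12.0 | 12.0 | 11.1 |
| Patient would have died before month 6 | 12.9 | 12.9 | 12.0 |

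With unrelated loss, exclusion does not inflate survival: over all the cases run it lowers the median by at most about 0.1 month against censoring. With informative loss, the main estimate is too high whether these patients are censored or excluded. What exclusion adds is the loss of the worst-case analysis, which returns the estimate to 12.0 only if the patients are still in the data. That analysis is a bound and not a correction: where loss is unrelated, it overshoots to 11.1.

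**The case against.** Nothing in the article ties scarcity to early death or short follow-up. A patient who dies at week 5 can have full baseline and treatment-day data and a death date, which is complete information for OS. The article lists sites failing to enter data first among the causes of missing data, so an almost empty record fits the rule at least as well. Read together, the rules may mean that short follow-up is handled by censoring and only unusable records are dropped. The threshold may stand in the full protocol or the analysis plan, neither of which is shown. The article also plans to report reasons for exclusion and to compare the groups.

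Much of this stands. A reader might infer that the plan discards early deaths, that survival is therefore inflated, or that the 6-week analysis is contradicted. The text supports none of these as fact. Recorded deaths are treated as events, inflation depends on who is removed, and the 6-week analysis can still be run on whoever remains. The extreme case, with every death before 3 months removed, would turn 12.0 into 15.0 months (12 + 3 under exponential survival), but no statement in the article points to it. The missing threshold is not a finding either.

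What the objection does not answer is the basis of the rule. Entry depends on the amount of data collected, for all endpoints, and no wording shields patients with short follow-up. The planned reporting and comparisons disclose a selection; none is stated to return the excluded patients to the risk set.

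**Conclusion.** The concern holds in a conditional form. The exclusion can select on early death or loss, fits poorly with the all-available-data and censoring rules, and can take away the patients for whom the 6-week worst-case analysis exists.

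Its size cannot be derived from the article. The rises in step 3 require that the excluded patients be the earliest deaths, that survival be exponential, and that 2% to 10% be excluded; all of these are assumptions. Where loss is unrelated to prognosis, there is no upward bias. The effect on adverse-event rates was not quantified.

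This should be fixed, but it is not critical. OS, PFS and safety are secondary objectives of a registry that calls itself descriptive and exploratory, and most items of the primary objective are recorded at baseline or on the treatment day.

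**What to change.** For time-to-event and safety analyses, define the set by facts known at treatment: eligible, consented, and a recorded date of first radioembolization. Make no exclusion for short or missing follow-up. Count every recorded death as an event, censor the others at the last date observed (possibly the treatment day), and apply the 6-week worst-case analysis to all of them.

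Confine any minimum-data requirement to individual descriptive tables, each stating the number missing. If results with exclusions are wanted, show them only as a sensitivity analysis.

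The cost is a change of wording. Survival and safety figures may become slightly less favourable. The gain has a limit: a patient censored on the treatment day adds nothing to the main Kaplan-Meier estimate, so the benefit for survival lies in keeping real early deaths and in letting the worst-case analysis cover all early losses.

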### Limitations

The single-arm observational study nature of the study design implies that several limitations need to be considered. The absence of a contemporaneous comparator group may limit our interpretation of the clinical data reported. Despite this, important positive features of the study are the long-term data collection for patients included and the valuable information collected on health-related QOL. The size of the study should enhance patient selection by providing new information on the patient subgroups that benefit most from this treatment in day-to-day clinical practice.

Furthermore, selection bias could occur at several stages of the study. An element of site selection was introduced when the Steering Committee created a list of sites that met the selection criteria of minimal expertise with radioembolization treatment. The potential of patient selection bias is addressed by a contractual agreed upon prospective design, whereby sites agreed to present the possibility to participate in the CIRT to all eligible patients consecutively.

Another source for bias relates to drop-out during follow-up. The sites included in the study have been advised to continue patient follow-up at least 24 months after the first treatment. However, patients may be lost to follow-up or withdraw their consent at any time. Loss to follow-up may relate to the course of disease or site procedures; for example, when a patient is treated at a participating site but followed-up by their referring physician, sometimes in another country. It will therefore not always be possible for study sites to collect additional follow-up data and the patient will be reported as lost to follow-up. Baseline characteristics will be compared between those lost to follow-up and those who have follow-up data to assess differences with the potential to bias results. Notable differences on a background characteristic will prompt additional analyses where the sensitivity of the results to that background characteristic will be further assessed.

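### Post-treatment procedures, later systemic chemotherapy and adverse events accrue over up to 24 months, but the stated summaries make no allowance for unequal observation time from loss to follow-up or withdrawal

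*Protocol article*

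**What the plan says.** Study Design and Objectives describes the primary objective by five items: "type of liver cancer, intention of treatment, prior hepatic procedures, associated systemic therapy, and postradioembolization hepatic procedures". Table 1 places part of this in the follow-up column: "Postradioembolization hepatic procedures Postradioembolization systemic chemotherapy". Adverse events of grades 1 to 5 are in the same column.

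Observation time differs between patients. Data Collection states: "The patient is then followed for a maximum of 24 months or until study exit". Limitations expects loss, for example when a referring physician takes over the follow-up: "It will therefore not always be possible for study sites to collect additional follow-up data and the patient will be reported as lost to follow-up". The same paragraph accepts that loss may be related to the course of the disease.

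For the primary end point and safety, Statistical Analysis plans this: "Data regarding the primary end point, safety, and technical considerations will be presented by summaries (eg, counts, means, standard deviations) and descriptive statistics". Kaplan-Meier and Cox methods are assigned to the time to event end points, and the censoring rules that follow are stated for the effectiveness analyses only. Outside quality of life nothing is imputed. Safety and effectiveness results, including those for subsequent procedures, are to be broken down by the Table 2 covariates.

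Three safeguards are planned: missing observations are counted in every summary table, patients with missing data are compared with those analysed, and patients lost to follow-up are compared at baseline with those followed. Notable differences in the last comparison lead to sensitivity analyses.

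**The concern.** The article sorts its end points into two classes. Those treated as time to event get censoring; the rest get descriptive summaries. Procedures and chemotherapy after treatment, and adverse events, are put in the second class although they depend on how long a patient was observed.

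If a patient lost at 3 months with no recorded procedure stays in the denominator of a 24-month proportion, that patient counts as free of a procedure for the whole period. The proportion then reflects completeness of follow-up as well as clinical practice. The same applies to late toxicity. Two subgroups with the same underlying rates could also show different percentages only because one was followed less completely.

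At stake are the forward-looking part of the primary objective and the safety tables. Tumour type, intention of treatment, prior procedures and prior systemic therapy are fixed by the day of treatment and are not affected.

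**Working it through.** The article states no incidence, death rate or loss rate on this point, so there is no figure to reproduce. The following is an illustration, and every rate in it is an assumption.

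**Inputs**
- Horizon T = 24 months (Data Collection).
- Death hazard d = ln 2 / median survival, with assumed medians of 9, 12 and 18 months.
- Event hazard h, set so that the 24-month risk in the absence of death is 10% or 30% (assumed).
- Loss hazard c, set so that loss by 24 months in the absence of death is 0%, 10%, 20% or 40% (assumed).
- Hazards are constant and independent.
- Administrative censoring is ignored: inclusion ended in December 2017 and follow-up in December 2019, so almost every patient had 24 months of potential follow-up.

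**Formulas**
- Cumulative incidence with death competing: h/(h+d) × (1 − exp(−(h+d)T)).
- Expected crude proportion over all patients: h/(h+d+c) × (1 − exp(−(h+d+c)T)).

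**One case in full** (median survival 12 months, event risk 30%, loss 40%)
- d = ln 2/12 = 0.0578; h = −ln(0.7)/24 = 0.0149; c = −ln(0.6)/24 = 0.0213 per month.
- Cumulative incidence: 0.0149/0.0726 × (1 − 0.175) = 16.9%.
- Crude proportion: 0.0149/0.0939 × (1 − 0.105) = 14.2%.
- Ratio 0.84. A simulation of 400,000 patients gave 16.9% and 14.1%, also a ratio of 0.84.
- Because death competes, 40% loss in the absence of death corresponds to about 23% of patients actually recorded as lost (ignoring the event itself).

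**Ratio of crude proportion to cumulative incidence over all assumed medians and event risks**

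| Loss by 24 months in the absence of death | Ratio |
|---|---|
| 0% | 1.00 |
| 10% | 0.96-0.97 |
| 20% | 0.91-0.93 |
| 40% | 0.82-0.85 |

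**Early events.** With the horizon cut to 3 months, an event risk of 20% in that time and the same loss hazards, the ratio is 0.97-0.99. With median survival 12 months and 40% loss, for example, it is 17.9% against 18.4%.

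**Subgroups.** Take two subgroups with the same event and death rates (median survival 12 months, event risk 30%), one with 10% loss and the other with 40%. The expected crude proportions are 16.3% and 14.2%, although the cumulative incidence is 16.9% in both.

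**Check on a tempting alternative.** One minus Kaplan-Meier with death censored would give 30% in the worked case, against 16.9%. That error is larger than the one to be repaired.

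**The case against.** The strongest reply is that the article fixes no wrong estimator. Its list of summaries is introduced as examples, no denominator is stated, and such detail may sit in the full protocol or analysis plan. Missing observations will be tabulated, so a patient lost early need not be counted as event-free. With a denominator restricted to patients with follow-up data, the direction of bias is not determined. This stands, and it is why the conclusion below is conditional. It does not remove the point, because the article does say which end points get censoring, and these outcomes are not among them.

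A second reply is that drop-out is openly named as a source of bias and is examined by baseline comparisons. These steps show the problem but do not correct a crude proportion. Also, a patient lost with no recorded procedure need not appear as a missing value.

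Third, the size is unknown. With 10% loss the effect is slight, and toxicity that occurs early is barely touched. Both are correct.

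Fourth, Table 1 lists a date only for effectiveness events, so event dates for procedures and adverse events cannot be taken for granted. This is also correct and limits the precision of the remedy.

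**Conclusion.** The point holds in conditional form. For outcomes that accrue during follow-up, the stated summaries make no allowance for unequal observation time. If all analysed patients are the denominator, crude 24-month proportions would be understated by about 3-4% in relative terms with 10% loss, 7-9% with 20% and 15-18% with 40%, but by only 1-3% for events in the first 3 months. These figures rest on constant, independent hazards and assumed rates. Informative loss, which the article considers possible, could change the size.

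Three stronger readings are not supported:

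- A reader might infer that deaths also depress the proportions. They do not. A patient who has died can no longer have a procedure, and with no loss the crude proportion equals the cumulative incidence at every death rate tried. Short survival affects interpretation, not bias.
- A reader might infer that understatement is certain. The open wording, the unstated denominator and the unknown loss rate do not allow that.
- A reader might infer that patients will be compared by whether they later had a procedure, with immortal-time bias. The breakdown uses Table 2, which contains no later procedure, so no such split is planned.

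**What to change.** For first hepatic procedure after treatment, first systemic chemotherapy after treatment and first adverse event of grade 3 or higher, report Aalen-Johansen cumulative incidence at fixed times, for example 3, 6, 12 and 24 months. Treat death as a competing event, censor at last contact, and show numbers at risk, overall and within the Table 2 subgroups. Keep the counts as a supplement, with the denominator stated and length of follow-up summarised. Do not use one minus Kaplan-Meier with death censored.

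Use event dates if they were recorded. Otherwise assign events to the 3-month follow-up interval, noting that sites set their own schedules.

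The method assumes that loss is unrelated to the later risk of the event, so the planned comparison of patients lost and followed should stay.

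The cost is a few sentences in the analysis text and some programming, with coarser timing if only intervals are available. No new data are needed provided that the timing of events was captured at least by visit.
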